### Evaluating patient eligibility

According to the inclusion and exclusion criteria, ECG, creatinine/eGFR, body weight and blood pressure measurements are required. The final decision on eligibility will be agreed with the treating physician on the ward. Capacity will be assessed and informed consent (and/or) assent obtained (see below).

### Inclusion and exclusion criteria

Patients with delirium or subsyndromal delirium will be included in this study by the study physicians. We will include patients with chronic cognitive impairment or dementia as well as patients free from dementia. Nursing home patients are eligible. Patients must be > 65 years old, though the average age is expected to be more than 80 years. Further, the patient must be willing and able to receive the study medication.

**Inclusion criteria**

All of the following conditions must apply to the prospective patient at screening prior to receiving study agent:Patient > 65 years old admitted to the acute, medical, geriatric wardDelirium or subsyndromal delirium within the last 48 hoursSigned informed consent from patient or relatives and expected cooperation of the patients for the treatment and follow up must be obtained and documented

**Exclusion criteria**

Patients will be excluded from the study if they meet any of the following criteria:Symptomatic bradycardia, bradycardia due to sick-sinus-syndrome, second- or third- degree AV-block (if not treated with pacemaker) or any other reason causing HR <50 bpm at time of inclusion [44].Symptomatic hypotension or orthostatic hypotension, or a systolic BP <120 at the time of inclusionIschemic stroke within the last 3 months or critical peripheral ischemiaAcute coronary syndrome, unstable or severe coronary heart disease (symptoms at minimal physical activity; NYHA 3 and 4) and moderate to severe heart failure (NYHA 3 and 4). (Acute coronary syndrome is defined according to international guidelines)A diagnosis of polyneuropathy, phaeochromocytoma or renal insufficiency (estimated GFR < 30 ml/min according to the MDRD formula) [44]Body weight <45 kgConsidered as moribund on admissionUnable to take oral medicationsCurrent use of tricyclic antidepressants, monoamine reuptake inhibitors or ciclosporinPreviously included in this studyAdverse reactions to clonidine or excipients (lactose, saccharose)Not speaking or reading NorwegianAny other condition as evaluated by the treating physician

### Informed consent and enrolment

Informed consent is a well-known challenge in studies of delirium [65,66], both due to the nature of delirium itself and the fact that people with underlying dementia are most at risk of developing delirium. Cognitively intact patients are included in this study on the basis of written, informed consent. We have developed a comprehensive information leaflet for cognitively intact patients and a simplified and shortened version for those who are partly or not at all competent to give their consent. For patients considered to lack capacity (due to severe delirium and/or dementia), but who are willing to take part, we will obtain proxy informed consent from a close relative. Consent to remain in the research will be obtained as soon as possible if capacity returns. Due to the importance of including patients as soon as possible after the diagnosis of delirium is made, the close relatives may give verbal consent (by phone) before randomisation and the written consent will be obtained as soon as possible after inclusion. We have good experience with this method from previous studies in our research group [67].

### Randomisation and blinding

The randomisation is based on computer-generated random numbers, and will be carried out by a statistician. The randomisation schedule will be distributed to the producer of the study medication, and capsules made accordingly. The randomisation will be stratified with respect to whether or not the patient was admitted from a nursing home, in order to balance the groups with respect to pre-admission cognitive decline, independence and comorbidity, all important prognostic factors.

### Study medication

Each capsule (CAPSUGEL) will contain either 75 μg Catapresan (clonidine hydrochloride) or 75 μg placebo, and will be produced and labeled by Kragerø tablettproduksjon A/S. The capsules containing active medication and placebo will look identical. If other medications are indicated for the treatment of delirium, the treating physician will prescribe this as “standard care”.

### Monitoring and safety

BP and HR will be monitored 3 hours after each loading dose (day 1) and then just before every dose. If there are signs of significant hypotension (systolic BP <100 mmHg) or bradycardia (heart rate <50 beats/min), further monitoring or treatment will be considered individually. During the whole treatment period blood pressure and heart rate will be assessed twice per day. ECG, serum creatinine, blood glucose and a clinical assessment by a physician (hydration, side-effects, RASS [61] and OSLA [62]) will be performed daily. Orthostatic BPtests will be performed during the hospital stay at day 5, 6 or 7 at 1100 (approximately 3 hours after administration of study drug).

For all patients, drug concentration (mean concentration just before intake and Cmax 3 hours after intake) will be measured at day 5, 6 or 7. The pharmacokinetics of clonidine varies inter-individually, possibly influencing individual treatment responses. But due to the short treatment period, measurement of drug concentration for individual drug modification is not feasible.

### Data collection

Demographic data, medical history, information regarding the acute underlying medical disease(s), drug use and proxy information will be collected during the hospital stay. Once included in the study, patients will be visited daily for efficacy and safety evaluations by the study physicians (geriatricians) or by the consultant on-call during the weekend.

We will assess pre-existent functional and cognitive status by asking the patient’s primary caregiver (the best available source) to complete questionnaires to assess the patient´s functional and cognitive state two weeks prior to hospital admission. Functional status will be assessed using the Barthel ADL Index [69] and the Nottingham Extended ADL Index (NEADL) [70]. To ascertain prior long-term cognitive decline we will use the Informant Questionnaire on Cognitive Decline in the Elderly (IQCODE) [71] and the Clinical Dementia Rating Scale (CDR) [72]. The Mini-Mental State Evaluation – Norwegian version (MMSE-NR) [73,74] will be performed at baseline and at discharge for the purposes of general cognitive screening. The Cornell Depression Scale [75,76] is based on proxy information and will be used to evaluate the degree of depressive symptoms.

Grip strength of the dominant hand will be measured using hand-held dynamometry once during the hospital stay and at follow-up after 4 months. The severity and number of comorbidities will be scored using the Cumulative Illness Rating Scale (CIRS) [77]. The level of physiological disturbance will be assessed by using Acute Physiology and Chronic Health Evaluation II (APACHE II) [78], the version utilising venous bicarbonate rather than arterial blood gases. Body Mass Index is registered as a marker of nutritional status.

We will use the algorithm described in the section above and in Table 4 to diagnose delirium (or subsyndromal delirium) according to the DSM-5 criteria.

We will also collect data about patient distress, using items from The Checklist of Nonverbal Pain Indicators (CNPI) [79]. Possible and suggestive causes of delirium are registered in each case at discharge.

### Laboratory tests and blood sample procedures

Data from routine blood samples taken at admission will be recorded (including Erythrocyte Sedimentation Rate, Haemoglobin, Leukocytes, Creatinine, Electrolytes, C-reactive protein, Albumin, Thyroid stimulating hormone and free Thyroxine levels).

All patients will have blood drawn for drug concentration levels at day 5, 6 or 7 (just before and 3 hours after intake of study medication), to be able to compare possible effects and side-effects to the actual plasma-concentration at the end of the trial.

Our study population is expected to have significant acute and chronic comorbidity. In this aspect, looking for new biomarkers is challenging, as we do not have a delirium-free control group. We will however take blood samples (serum and plasma) for biomarkers at inclusion, at mid-stay (day 3–5) and at discharge, to explore markers already known to be associated with delirium. Interesting biomarker candidates include S100B [80,81], neopterin [82], IGF-1 [83], MMP-9, protein C, sTNFR1 [84]. The serum and plasma will be stored in a biobank freezer at Oslo University Hospital together with blood stored in EDTA tubes for possible DNA-analyses.

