### Alpha-2-adrenoreceptor agonists

Dexmedetomidine and clonidine are both alpha-2-adrenoceptor agonists activating presynaptic inhibitory alpha-2-adrenoreceptors. Clonidine is a partial agonist with an alpha-2a-to-alpha-1 selectivity ratio of 39. For dexmedetomidine this ratio is 1300 [28]. They exert a general inhibitory influence on the sympathetic nervous system, in particular due to CNS effects [29]. Dexmedetomidine decreases sympathetic activity and attenuates the hemodynamic and neuroendocrinal stress responses (including of cortisol), resulting in decreased heart rate (HR) and blood pressure (BP) as well as sedative and analgesic effects [30]. In the intensive care setting, both substances reduce the need for opioids and sedatives [31]. Dexmedetomidine is increasingly used in intensive care patients, and is also used as an adjuvant during regional anaesthesia. Recently conducted studies indicate that the incidence of delirium is lower in intensive care patients receiving dexmedetomidine than in those receiving benzodiazepines [32,33], propofol [34] or morphine [35]. Currently available evidence thus suggests that dexmedetomidine may have value in the prevention and treatment of delirium in the intensive care unit [36,37]. Indeed, it is now in clinical use in the USA and Europe [38].

Most patients with delirium are however treated outside of intensive care units, where intravenous use of dexmedetomidine is not feasible. An alternative agent might thus be orally administred clonidine, which has very similar pharmacodynamics to that of dexmedetomidine [31], even though its alpha-2 selectivity is somewhat lower [28]. Clonidine additionally has an independent stimulatory effect on the parasympathetic activity and a slight anti-inflammatory effect [39,40], further making it an interesting candidate for delirium treatment. This does also accord with the hypothesis of delirium as a consequence of aberrant stress responses [13].

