**Primary**	
Delirium trajectory	MDAS
**Secondary** (also with subanalyses for subsyndromal delirium and hypoactive/hyperactive/mixed delirium)	
Time-to-first delirium resolution	DSM-5
Incidence of “full-scale” delirium	DSM-5
Severity of delirium	MDAS, OSLA
Delirium subtype	MDAS, OSLA, DelApp
Use of “rescue medication”/additional drugs (as other sedatives, analgetics and antipsychotics)	Registration of use of all medication
Length of hospital stay	Registrations
Patient distress	Checklist of Nonverbal Pain Indicators
Cognitive function in follow-up after 4 months	MMSE-NR, Clock drawing test, Ten-words memory test, Trial making test A and B, IQCODE, CDR
Independence in follow-up after 4 months	Barthel ADL, NEADL
Pharmacokinetic response to clonidine	Serum drug concentrations
Pharmacodynamic response to clonidine	BP, HR, ECG, RASS, OSLA, symptoms of bradycardia, orthostatic hypotension or other side-effects
Biomarkers	Blood samples
Institutionalisation	Registrations
Survival	Registrations

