### Secondary endpoints

We will compare the actively treated group with the placebo group with respect to secondary endpoints shown in Table 2. The main secondary endpoint is the duration of delirium monitored daily by the DSM-5 diagnostic criteria. We will also study the feasibility of oral clonidine in a geriatric ward and effects of clonidine upon a variety of outcomes as a means to design a potentially more definite study later. We will do per protocol analyses and exposure-response analyses based on plasma-concentration.

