## Methods and design

### Study design

The Oslo Study of Clonidine in Elderly Patients with Delirium (LUCID) is a randomised, placebo-controlled, double-blinded, parallel group study with 4 month prospective follow-up (Figure 1). We aim to include 100 inpatients with delirium (or subsyndromal delirium) in an acute geriatric ward. Patients will be randomised to orally administrated clonidine or placebo until delirium free (by DSM-5 criteria) or no subsyndromal delirium for 2 days, or after a maximum of 7 days treatment. If the treating physician plan to discharge the patient (still having delirium/subsyndromal delirium), before 7 days, we will end the treatment 24 hours before discharge. Assessment of haemodynamics (blood pressure, heart rate and ECG) and of delirium will be performed daily until discharge, or a maximum of 7 days after end of treatment.

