### Statistical analysis

The primary endpoint is the repeated measurements of MDAS over time. Differences in the MDAS trajectories between the treatment groups will be analysed by a mixed linear model. In addition we will, as a secondary endpoint, compare the time to resolution of delirium as measured by DSM-5. The Kaplan Meier method and the logrank test will be applied. In addition a Cox proportional hazards model will be applied to estimate hazard ratios. The additional different secondary endpoints will be analysed by t-tests when variables are continuous and by chi-square tests when variables are categorical. Patient survival will be compared between groups by the logrank test and Cox proportional hazards model.

For the comparison of the MDAS trajectories no adjustment for multiplicity will be applied. If a statistically significant difference between the MDAS trajectories is demonstrated, analyses of secondary endpoints will be performed without any formal adjustment for multiplicity. If any conclusion on efficacy is to be drawn based on a secondary endpoint only, a simple Bonferroni adjustment (dividing the 5% level with the actual number of tests performed) will be applied. If the use of additional antipsychotics differs between treatment groups, the amount calculated as haloperidol equivalents [68] will be included in the statistical model.

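### If the biomarker endpoint is compared between arms on the discharge sample, the result could mix a drug effect with differences in sampling day and time off drug; the day 3–5 sample is the safer basis.

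*Protocol article*

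**What the plan says.** Four statements in the protocol article bear on this point.

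- Table 2 lists biomarkers as a secondary endpoint, measured by blood samples, with no time point.
- Under Secondary endpoints: "We will compare the actively treated group with the placebo group with respect to secondary endpoints shown in Table 2".
- Under Statistical analysis: "The additional different secondary endpoints will be analysed by t-tests when variables are continuous". No covariate or sampling day is mentioned for these tests.
- Under Laboratory tests and blood sample procedures, serum and plasma for biomarkers are taken "at inclusion, at mid-stay (day 3–5) and at discharge". The stated aim is "to explore markers already known to be associated with delirium".

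Two further statements determine what a discharge sample represents. Table 2 also has "Length of hospital stay" as a secondary endpoint. Under Study design, treatment runs "until delirium free (by DSM-5 criteria) or no subsyndromal delirium for 2 days", or for at most 7 days; for a patient due to leave before day 7 with delirium or subsyndromal delirium still present, "we will end the treatment 24 hours before discharge".

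**The concern.** Of the two samples taken after inclusion, one has a near-common study day and the other is tied to an event after randomisation. A t-test on the second compares patients at whatever day they happened to leave. If stay differs between arms, the arms are sampled at different distances from the acute illness.

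Time off drug varies as well. One patient may be sampled a day after the last dose and another several days after it, depending on how the delirium resolved. Patients who die in hospital drop out of the discharge comparison altogether, and survival is also a Table 2 endpoint.

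What is at stake is how an exploratory result is read. The article says that there is no delirium-free control group, so the randomised contrast is the only controlled comparison available for these markers. The Background credits clonidine with "a slight anti-inflammatory effect", so a difference in these markers, or the lack of one, could easily be given a mechanistic meaning that the sampling times do not support.

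**Working it through.** The plan gives no figure on this point to reproduce, so the check has two parts.

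**1. What differs between the two post-inclusion samples**

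| | Day 3–5 sample | Discharge sample |
|---|---|---|
| Study day | within a 3-day window for everyone still in hospital | set by length of stay |
| Can treatment move the day? | hardly | yes, if it changes stay |
| Time off drug | none or short | varies with recovery and discharge plan |
| Who has no value | patients discharged or dead before the window | patients who die in hospital |

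Time off drug is not trivial. The article gives an elimination half-life of 5 to 25.5 hours. Twenty-four hours without drug is therefore 24/25.5 = 0.9 to 24/5 = 4.8 half-lives, and patients who stay on after treatment ends have longer.

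**2. How large a spurious difference could be (illustration only)**

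All inputs are assumptions, because the article gives no biomarker SD, no time course and no expected difference in stay:

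- log-scale SD 0.8;
- 50 per arm (100 patients in all; the overall allocation ratio is not stated), all with a sample;
- no drug effect on the marker;
- marker falling by a fraction *f* per day;
- mean stays differing by *d* days.

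Formulas:

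- Spurious log difference: *b* = *d* × [−ln(1 − *f*)]; false ratio = exp(*b*)
- Standard error: 0.8 × √(2/50) = 0.16
- Two-sided rejection at 5%: P(Z > 1.96 − *b*/0.16) + P(Z < −1.96 − *b*/0.16)

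Worked case, *d* = 2 and *f* = 10%: *b* = 2 × 0.1054 = 0.211; ratio 1.23; *b*/0.16 = 1.317; rejection = P(Z > 0.643) + P(Z < −3.277) = 26%.

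| Fall per day | 1-day difference: rejection | 2-day difference: false ratio | 2-day difference: rejection |
|---|---|---|---|
| 5% | 6% | 1.11 | 10% |
| 10% | 10% | 1.23 | 26% |
| 15% | 17% | 1.38 | 53% |

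A second parameterisation, with the slope in SD units per day and a standard error of √(2/50) = 0.2 SD, shows the same pattern. For differences in stay of 1, 2 and 3 days, a slope of 0.05 SD per day gives 5.7%, 7.9% and 11.7%; 0.1 SD per day gives 7.9%, 17.0% and 32.3%; 0.2 SD per day gives 17.0%, 51.6% and 85.1%. If either the slope or the difference in sampling day is zero, rejection is 5.0%. The bias therefore needs both, and sampling on a common day removes this component of it.

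**The case against.** The strongest reply is that the article never makes the discharge sample the one compared. It lists three samples, names no time point in Table 2 and gives one general t-test rule. Which sample carries a secondary comparison, and with what adjustment, is commonly left to a full protocol or analysis plan that is not shown. This stands. A reader might infer that the plan fixes a comparison at discharge, and the text does not support that.

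A reader might also infer a direction: that a shorter stay under clonidine would leave its patients with higher inflammatory values and so mask a benefit. The article does not support that either. It gives no time course for any candidate marker. If patients left sooner because they recovered sooner, the arms could be sampled at a similar clinical state. The anti-inflammatory remark is background on the choice of drug, and no passage says that the biomarkers will test it.

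The rejection rates rest wholly on assumed inputs, and the higher ones need the 2-day difference with the steeper falls. The 5% reference level applies only when the primary result is significant; an efficacy conclusion resting on a secondary endpoint alone is to be Bonferroni-adjusted. The Discussion also calls the secondary objectives exploratory.

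The combination that the article does state survives all this: a between-arm endpoint, an unadjusted t-test, and one of two post-inclusion samples tied to discharge. Nothing in it rules out the weaker comparison, and an unadjusted t-test makes no use of the inclusion value already collected.

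**Conclusion.** The point holds as a conditional caution and a cheap improvement. It is not an error in the plan. If discharge biomarker values are tested between arms, the result could mix a drug effect with days since inclusion and time off drug, and it would leave out in-hospital deaths. Neither direction nor size can be derived from the article. The 6% to 53% range shows only what assumed differences in stay of 1 to 2 days and assumed falls of 5% to 15% per day would do to a nominal 5% test. It would be going too far to say that a difference in stay will appear as a biomarker difference, because that needs a real difference in stay and a marker with a time trend, and the article establishes neither. The consequence is confined to an exploratory secondary endpoint; the primary MDAS analysis is unaffected.

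**What to change.** State in the analysis plan that the exploratory between-arm biomarker comparison uses the day 3–5 sample, by a linear model with treatment arm and the inclusion value as covariate (on the log scale where the marker is skewed), in place of the unadjusted t-test. Report discharge values descriptively by study day, without a test between arms, and give the number of patients in each arm without a discharge sample because they died in hospital.

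The cost is a sentence or two of text. No new blood, visits or patients are needed, since both samples are already planned. The downside is that patients discharged before day 3 have no mid-stay value; their number should be reported by arm. If an existing analysis plan already names the day 3–5 sample, the sponsor need only confirm it.

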### Follow-up assessments

We will phone the patient or care-taker by phone one week after the end of the treatment to consider possible side-effects/ rebound effects or relapse of the delirium. No physical examination or psychometric tests will be performed. We will register the level of care, and whether the patient has been discharged home or to an institution.

Four months after discharge, a home visit will be done to perform cognitive tests (see Table 2). Based on proxy information, we will evaluate each patient´s level of independence and functional and cognitive status. We will assess the presence of persistent delirium (according to DSM-5 criteria) and subsyndromal delirium and perform the MDAS. Grip strength will be measured. Level of care, any readmissions to hospital and cumulative mortality will be registered.. Causes of death will be ascertained from the Cause of Death Register.

### Criteria for patient discontinuation

Patients may be discontinued from study treatment and assessments for several reasons. These include: omission of more than 3 following dosages, voluntary discontinuation by the patient, safety reasons as judged by the study physician or treating physician, or significant non-compliance with the protocol as judged by the study physician. Any patient withdrawn from the study will be included in the statistical intention-to-treat analysis. If possible, a final assessment shall be made (end of study visit) and the reason for discontinuation shall be recorded. Progression of delirium is not a discontinuation criterion, as the trajectories are variable and impossible to predict. Progression of delirium may however make the patient unwilling to further participate. If any of the exclusion criteria appear during the treatment, treatment will be discontinued. (Except changes in blood pressure and heart rate, which will be managed as described in the dosage plan).

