### Sample size, statistical power and statistical analysis

Based on the expected number of patients fulfilling the inclusion criteria within 36 months a sample size of n = 100 was chosen. Inclusion of 100 patients would lead to a power of only 71% to detect an absolute treatment difference of 25% in proportion recovered according to DSM-% (40% vs 65%). Correspondingly, using MDAS at one single point in time as the response measure would lead to approximately 80% power assuming a standard deviation of 9 and a difference in mean MDAS score of 5. Thus, analyzing treatment efficacy at only one point in time would lead to low power. An analysis of repeated measurements will reduce random variability and thereby increase power. The primary analysis is therefore a mixed linear model taking all MDAS measurements into account.

The expected efficiency gain is difficult to estimate precisely, but assuming a standard deviation of 9 on the MDAS and a correlation between measurements of r = 0.5, the power would be around 95% to detect a mean MDAS difference of 5 or a power of 80% to detect a mean difference of 3.5 between groups.

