## Discussion

Delirium is a severe and common condition among acute hospitalised elderly patients, and the options for pharmacological treatment are sparse. To our knowledge, no randomised placebo controlled trial investigating treatment of delirium with clonidine or other alpha-2-adrenoreceptor agonists has yet been done in non-critically ill medical patients. It has been recommended [85,86] that future studies on pharmacological treatment of delirium should have less restrictive exclusion criteria, in order to avoid low external validity. Further, future studies should ensure stratification according to known underlying risk factors for delirium. The trials should then have a true placebo arm and use validated instruments for delirium assessments. We have planned this trial according to these guidelines.

The results of our study will be more clinically relevant if the medication is easy and safe to administer to patients in a general ward, without the need for invasive monitoring. Frail and demented patients are more prone to develop delirium, and the treatment regimen should be feasible for this large group of patients. Thus, it is important that the exclusion criteria are not too strict, and we will therefore include patients with dementia and patients from nursing homes in this trial.

Delirium is a clinical diagnosis, based on history, information from proxies, mental status examination and evaluation of an underlying medical cause. There is no single simple test, neither psychometric nor physiological, to ascertain delirium. We have described the procedure that we will use to make the final diagnosis according to the DSM-5 criteria. All assessments of delirium will be made by the investigators (geriatricians trained in delirium evaluation) during weekdays, and by geriatricians on call in the weekends.

The primary outcome in this study is the trajectory of delirium, measured daily by MDAS. Due to features common in studies of delirium (small sample sizes, sample attrition, fluctuation course of the disease and spontaneous recovery), techniques that use all available data and take a global (as opposed to end-of-trial) perspective are preferred [87]. Using longitudinal trajectories as the main outcome will almost always have greater power than end-of-trial analyses [87-89], as well as reducing the problem with missing data.

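### Dose omission, safety stops and non-compliance may end the in-hospital delirium assessments along with study drug, although the primary analysis relies on every MDAS score

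*Protocol article*

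**What the plan says.** Criteria for patient discontinuation gives a single list of grounds: "Patients may be discontinued from study treatment and assessments for several reasons. These include: omission of more than 3 following dosages", followed by voluntary discontinuation, safety reasons judged by a physician, and significant non-compliance with the protocol. It continues: "Any patient withdrawn from the study will be included in the statistical intention-to-treat analysis. If possible, a final assessment shall be made". That assessment is labelled an end-of-study visit.

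The same section treats one situation differently. If an exclusion criterion appears during treatment, "treatment will be discontinued. (Except changes in blood pressure and heart rate, which will be managed as described in the dosage plan"; assessments are not mentioned there.

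The Study design section sets the schedule: assessment of haemodynamics "and of delirium will be performed daily until discharge, or a maximum of 7 days after end of treatment".

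The scores feed two endpoints. On the first, the sample size section says "The primary analysis is therefore a mixed linear model taking all MDAS measurements into account". On the second, "The main secondary endpoint is the duration of delirium monitored daily by the DSM-5 diagnostic criteria". The Discussion explains the choice of a trajectory endpoint: "techniques that use all available data and take a global (as opposed to end-of-trial) perspective are preferred".

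**The concern.** A patient's wish to leave can rightly end both drug and assessments. Omitted doses, a safety stop or poor adherence to the capsules are reasons to stop the drug; they do not by themselves stop anyone measuring delirium. The discontinuation section nevertheless lets these grounds end both, whereas the Study design section plans off-drug daily assessment.

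The scores lost this way need not be a random subset. Table 1 holds doses for systolic pressure below 100 mmHg, heart rate below 50 or RASS of −3 or less. The background sections describe hypotension, bradycardia and sedation as clonidine effects. The discontinuation section also says "Progression of delirium may however make the patient unwilling to further participate", so leaving can be linked to the outcome itself.

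A linear mixed model in effect predicts the missing days from the patient's earlier scores and from patients in the same arm who were still observed, on or off drug. That is valid if the scores are missing at random given what was observed. Keeping a patient in the intention-to-treat set does not create scores that were never collected, and no analysis plan can recover them. The daily DSM-5 series behind delirium duration loses the same days.

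**Working it through.** **The plan's own figure.** Inputs from the sample size section: n = 100 (50 per arm assumed), SD 9, r = 0.5. Two-sided 5% is assumed. With 7 daily scores, the SD of a patient's mean is 9 × √((1 + 6 × 0.5)/7) = 6.80, and the standard error of the difference is 6.80 × √(2/50) = 1.361. Power for a difference of 5 is then 95.7%, in line with the stated figure of around 95%. For 3.5 points this formula gives 73.0%, not the stated 80%. Nothing here depends on that; 3.5 serves only as a yardstick.

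**Timing.** Count maintenance doses only. More than 3 consecutive omissions means 4: day 2 morning and evening, day 3 morning and evening. At the earliest, days 1–3 are observed and days 4–7 of a 7-day window are at risk. Safety or non-compliance stops have no such earliest day.

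**Assumed inputs (the protocol gives none).** A share p of one arm stops at that point, and nobody is discharged within the 7 days. From day 4 their true MDAS lies d points above what the model predicts. Range: p from 0.06 to 0.20, d from 3 to 5.

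**Formulas.**
- No final assessment: bias in the 7-day mean = p × d × 4/7; bias on day 7 = p × d.
- Final assessment on day 4: each of the 4 observed scores gets weight 0.5/(1 + 3 × 0.5) = 0.2 in predicting a later day, so 0.8 of the excess stays unseen on days 5–7. Bias in the 7-day mean = p × d × 0.8 × 3/7; bias on day 7 = 0.8 × p × d.

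**Results, only clonidine patients stopping (MDAS points in favour of clonidine).**

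| p | d | 7-day mean, final assessment | 7-day mean, none | Day 7, final assessment | Day 7, none |
|---|---|---|---|---|---|
| 0.06 | 3 | 0.06 | 0.10 | 0.14 | 0.18 |
| 0.10 | 5 | 0.17 | 0.29 | 0.40 | 0.50 |
| 0.20 | 5 | 0.34 | 0.57 | 0.80 | 1.00 |

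Against 3.5 points, the 7-day figures are 2–10% with the final assessment and 3–16% without. A generalised least squares simulation (4000 trials per scenario) agrees to within 0.01.

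**Sensitivity (d = 5, final assessment made).**
- Clonidine 20%, placebo 10%: (0.20 − 0.10) × 5 × 0.8 × 3/7 = 0.17.
- 20% in both arms: 0.
- Placebo only, 20%: 0.34 against clonidine.
- Clonidine 20%, days 1–5 observed before the stop: 0.12 with the final assessment, 0.29 without.

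If stopped patients do as predicted (d = 0), the bias is 0.

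**Precision.** If 20% of one arm stops after day 3 with no final assessment, the standard error rises from 1.361 to 1.373. If 10%, 20% or 30% of all patients have only 2 of 7 scores, power for 5 points goes from 95.7% to 95.3%, 94.8% or 94.3%. The issue is bias, not power.

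**The case against.** The best defence is that the two sections can be read together. The verb is permissive, the list also contains voluntary withdrawal, and the end-of-study visit may be meant only for patients who leave altogether. The Study design section makes no exception for an early end of treatment, and this is a condensed article. That is a fair account of what the authors may have intended. It does not remove the problem: the listed grounds are attached to treatment and assessments jointly, while a few lines later an exclusion criterion stops treatment alone. A site following the text could stop measuring.

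Several limits stand:
- A reader might infer that a stopped patient has no further MDAS. Follow-up assessments plans one at 4 months and does not exclude patients who stopped drug. The loss concerns the in-hospital daily series. The one-week telephone call includes no psychometric tests, so it does not replace that series.
- A reader might infer that the model fills gaps only from patients still taking the drug. Patients whose treatment ended after 2 delirium-free days are also assessed off drug.
- Non-compliance is with the protocol, so it can include refusing the daily tests, and that may rightly end assessments.
- Blood pressure and heart rate changes are handled by holding and rechecking, and patients enter with systolic pressure of at least 120 mmHg and heart rate of at least 50. More than 3 consecutive holds may be uncommon. The exception is attached to the exclusion-criteria sentence, however, and mentions neither RASS holds nor refused doses.
- The bias figures rest on assumed, one-sided, early stopping without discharge. With the final assessment, the largest is about a quarter of the standard error (0.34/1.361 = 0.25); without it, about 0.4 (0.57/1.361 = 0.42).

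**Conclusion.** The point holds as a badly fixed rule. The discontinuation section allows drug-related stops to end in-hospital delirium assessment, against the daily schedule in Study design and against the stated aim of using all MDAS scores.

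Two stronger readings are tempting and unsupported. The text does not require assessments to stop. Nor does it show that the trial would favour clonidine: it reports no hold frequency, no difference between arms and no outcome of stopped patients.

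Under the assumptions above, the bias in the 7-day mean is about 0.06 to 0.57 points if only clonidine patients stop early, zero if stopping is balanced, and reversed if only placebo patients stop. That is modest, with negligible loss of power. The change is still worth making, because unmeasured days cannot be recovered later and measuring them is already planned. Confidence is medium, given the permissive wording.

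**What to change.** Reword the opening of Criteria for patient discontinuation so that omission of more than 3 consecutive doses, safety stops and non-compliance with study medication end study drug only. State that daily MDAS and DSM-5 assessments then continue on the Study design schedule (until discharge, or at most 7 days after end of treatment), and end early only if the patient or proxy withdraws from assessments or the patient refuses them. Reserve the final assessment, where possible, for those patients.

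The cost is one reworded sentence. No visits are added, because these daily assessments are already scheduled.
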